## 6.6 Dose Modification and Stopping/Suspension Rules

An IDMC will be established and an IDMC charter agreed prior to screening of any subjects for the study. The IDMC charter will describe the role and responsibilities of the IDMC and will reflect the stopping/suspension rules described in this section. The IDMC will review the safety of study subjects throughout the study as described in the IDMC charter. At pre-specified time points described in this section, the IDMC will do a formal review of available data and make a recommendation with supporting rationale to the Sponsor who will act accordingly. There are currently no stopping/suspension rules foreseen in Part 2, however the IDMC will be requested to specify in their recommendation after Part 1, if these should be implemented. If so, then the IDMC should endorse a sponsor proposal or make a proposal for such stopping/suspension rules for Part 2.

Occurrence of below noted serious adverse reactions or Grade  $\geq 3$  treatment-related AEs will be considered irrespective of whether or not they are in the same system-organ-class.

### **6.6.1 Dose Escalation and Stopping/Suspension Rules During Part 1**

Two subjects in Cohort 1 will act as sequential sentinel subjects with at least 24 hours between the treatment of the first and the second sentinel subject. Each sentinel subject will be closely monitored for 24 hours after receiving XVR011. The Sponsor will confirm that relevant adverse reactions as defined below have or have not occurred in this 24-hour period.

- If neither of the two sentinel subjects experience any serious adverse reactions (i.e. SAEs considered at least possibly related to the treatment) and if at most 1 sentinel subject experiences a Grade  $\geq 3$  treatment-related AE during this period, then after sponsor review, the remaining 7 subjects will be enrolled and treated.
- If one or more of the two sentinel subjects experience a serious adverse reaction or if both sentinel subjects experience a Grade  $\geq 3$  treatment-related AE, enrolment will be suspended pending a review of the data by the IDMC, who will make a recommendation regarding study continuation.
- If at any point during the Cohort, serious adverse reactions are reported in 1 or more subjects, or Grade  $\geq 3$  treatment related AEs are reported in 2 or more subjects, enrolment will be suspended pending the outcome of an IDMC review.

After all 9 subjects are enrolled and treated in Cohort 1 and the last subject has been treated and monitored for 24 hours, the sponsor will confirm that all relevant adverse reactions as defined below are reported.

- If 1 or more of the 9 subjects in Cohort 1 experience a serious adverse reaction, or if 2 or more of the 9 subjects experience a Grade  $\geq 3$  treatment-related AE, the IDMC will review available data to make a recommendation on starting Cohort 2.
- If no subject has experienced a serious adverse reaction and if  $< 2$  subjects have experienced a Grade  $\geq 3$  treatment-related AE in Cohort 1, enrolment in Cohort 2 will start after sponsor review only.

In any case, the first two subject enrolled in Cohort 2 will be sentinel subjects, and the enrolment of the subjects will follow the same rules as for Cohort 1.

After all 9 subjects are enrolled and treated in Cohort 2 and the last subject has been treated and monitored for 24 hours, the sponsor will confirm that all relevant adverse reactions as defined below are reported.

- If 1 or more of the 9 subjects in Cohort 2 experience a serious adverse reaction or, if 2 or more of the 9 subjects experience a Grade  $\geq 3$  treatment-related AE, the IDMC will review available data to make a recommendation on starting Cohort 3.
- If no subject has experienced a serious adverse reaction and if  $< 2$  subjects have experienced a Grade  $\geq 3$  treatment-related AE in Cohort 2, enrolment in Cohort 3 will start after sponsor review only.

In any case, the first two subject enrolled in Cohort 3 will be sentinel subjects, and the enrolment of the subjects will follow the same rules as for Cohort 2.

### 6.6.2 Dose Selection for and Start of Part 2

A phase 1a study (protocol EXEVIR0102) in healthy subjects is being conducted in parallel with part 1 of this study. It is evaluating the same dose levels, namely 250, 500 and 1000 mg as a single IV infusion in a dose ascending design, with a placebo control. Per dose level, 8 subjects receive a single IV infusion of XVR011 and 2 subjects receive a single IV infusion of placebo in a blinded manner. The study will generate PK data and safety data not confounded by the disease state. An interim analysis of study EXEVIR0102 will be performed when all dose groups have received treatment and when the last dose group (1000 mg) has completed the 8-day follow-up. As discussed in section 4.3 Justification for Dose, the main driver for the dose determination is the target serum concentration and number of days this is exceeded, in addition to safety. The PK parameters from the healthy subjects are considered predictive for the patient setting. The safety profile will be reviewed of the 3 different dose levels in the healthy subject study.

The IDMC will be asked to make a recommendation to progress to Part 2 (Phase 2 design) of this study with the recommended dose based on the interim analysis of the Phase 1a study in 30 healthy subjects, supplemented with the available data from Part 1 of this study, even if not all Part 1 cohorts have reached the planned enrolment. This is due to recruitment challenges in Part 1 of this study resulting from low hospitalisation rate and reluctance of sites to participate and enrol patients in a Phase 1 clinical study.

## **6.7 Discharge from the Hospital and Follow-up**

Subjects may be discharged from hospital at the earliest 24 hours after study treatment administration and at the Investigator's discretion if their condition improves. All Visit 3 (Day 2) assessments must be performed before hospital discharge.

Study assessments will be performed every day up to Day 4 and then weekly until Day 29. For Part 2 there are 2 additional visits, namely on Day 60 and Day 90. After discharge from hospital, subjects will return to the study site for each per protocol study visit until the EOS (Day 29 for Part 1 / Day 90 for Part 2).

Subjects who are discharged from hospital before the EOS (Day 29 for Part 1 and Day 90 for Part 2) and outside the per protocol planned visit schedule must have an additional visit to perform the discharge assessments.

Subjects who are discharged from the hospital before the EOS (Day 29 for Part 1 and Day 90 for Part 2) on the day of a per protocol planned visit (e.g. Day 2, Day 3, Day 4, Day 8, Day 15, Day 22, Day 29 (part 2 only) and Day 60 (part 2 only) must have the discharge assessments done in addition to the per protocol planned visit assessments if not yet covered (assessments only need to be performed once).

## **6.8 Treatment After the End of the Study**

After the end of the study, no further treatment with XVR011 is expected. Subjects will continue receiving SoC treatment as clinically indicated.

## **7 Discontinuation of Study Treatment and Subject Discontinuation**

### **7.1 Discontinuation of Study Treatment**

Study treatment is administered as a single IV infusion on Day 1. This infusion must be permanently stopped in case of Grade 3 or 4 infusion related reactions (see Section 6.1).

### **7.2 Subject Discontinuation/Withdrawal from the Study**

A subject may withdraw from the study at any time at his/her own request or may be withdrawn at any time at the discretion of the Investigator for safety, behavioural, or administrative reasons. The subject will be definitively discontinued from both the study treatment and the study at that time.

If the subject withdraws consent for disclosure of future information, the Sponsor may retain and continue to use any data collected before such a withdrawal of consent.

If a subject withdraws from the study, he/she may request the destruction of any samples taken and not tested, and the Investigator must document this in the site study records.

At the time of discontinuing from the study, if possible, an early discontinuation (ED) visit should be conducted, as shown in the SoA. Refer to the SoA for data to be collected at the time of study discontinuation and follow-up and for any further evaluations that need to be completed.

When a subject participation has been terminated prior to completing the study, the reason is recorded as follows:

- Pregnancy
- Adverse event
- Treatment failure
- Protocol violation
- Lost to follow-up
- Subject withdrew consent at own request
- Other

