### **7.3 Loss of Subjects to Follow-Up**

A subject will be considered lost to follow-up if he or she repeatedly fails to return for scheduled visits and is unable to be contacted by the study site.

The following actions must be taken if a subject fails to return to the clinic for a required study visit:

- The site must attempt to contact the subject and reschedule the missed visit as soon as possible (and within the visit window, where one is defined) and counsel the subject on the importance of maintaining the assigned visit schedule and ascertain whether or not the subject wishes to and/or should continue in the study.
- In cases in which the subject is deemed lost to follow-up, the Investigator or designee must make every effort to regain contact with the subject (where possible, 3 telephone calls and, if necessary, a certified letter to the subject's last known mailing address or local equivalent methods). These contact attempts should be documented in the subject's medical record.
- Should the subject continue to be unreachable, he/she will be considered to have withdrawn from the study.

Discontinuation of specific sites or of the study as a whole is handled as part of the appendix on Governance, Appendix 1, Section 10.1.9.

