**Table 9–2 Populations for Analysis**

| Population (Analysis Set)               | Description                                                                                                                                                                                                                                                                                                                                                                                     |
|------------------------------------------------|--------------------------------------------------------------------------------------------------------------------------------------------------------------------------------------------------------------------------------------------------------------------------------------------------------------------------------------------------------------------------------------------------------|
| Enrolled Analysis Set (EAS)                    | All subjects who signed the ICF (including screening failures).                                                                                                                                                                                                                                                                                                                                        |
| Full Analysis Set (FAS)                        | The FAS is defined under an intent-to-treat population principle.
Part 1: The FAS comprises all subjects to whom study treatment has been dispensed.
Part 2: The FAS comprises all subjects to whom study treatment has been randomised. Statistical analyses will be based on study treatment groups as per randomisation, irrespective of the study treatment actually received. |
| Per Protocol Analysis Set (PPS), if applicable | Part 1: The PPS comprises all the FAS subjects who received study treatment.
Part 2: The PPS comprises all the FAS subjects who received study treatment and have a positive RT-PCR test at baseline (central laboratory). In both Part 1 and Part 2, a subject will be completely excluded from the PPS in case of protocol deviations affecting study analyses.                     |

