### **Female Subjects Who Become Pregnant**

- The Investigator will collect pregnancy information on any female subject who becomes pregnant while participating in this study. Information will be recorded on the appropriate form and submitted to the Sponsor within 24 hours of learning of a subject's pregnancy. The subject will be followed to determine the outcome of the pregnancy. The Investigator will collect any follow-up information on the subject and the neonate and the information will be forwarded to the Sponsor. Generally, follow-up will not be required for longer than 6 to 8 weeks beyond the estimated delivery date. Any termination of the pregnancy will be reported, regardless of foetal state (presence or absence of anomalies) or indication for the procedure.
- While pregnancy itself is not considered to be an AE or SAE, any pregnancy complication or elective termination of a pregnancy will be reported as an AE or SAE. A spontaneous abortion is always considered to be an SAE and will be reported as such. Any post-study pregnancy-related SAE considered reasonably related to study treatment by the Investigator will be reported to the Sponsor as described in Section 8.3.4. While the Investigator is not obligated to actively seek this information in former study subjects, he or she may learn of an SAE through spontaneous reporting.

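### When the investigator withdraws a subject, Section 7.2 ends outcome collection as well, although treatment is a single Day 1 infusion and the Part 2 analysis covers all randomised subjects over 28 days

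*Protocol*

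**What the plan says.** Section 7.1 states that treatment is a single infusion on Day 1. Under Section 7.2 a subject can leave at their own request, or "may be withdrawn at any time at the discretion of the Investigator for safety, behavioural, or administrative reasons". In either case: "The subject will be definitively discontinued from both the study treatment and the study at that time".

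For data at exit, Section 7.2 says: "At the time of discontinuing from the study, if possible, an early discontinuation (ED) visit should be conducted, as shown in the SoA". Part 2 (Table 1–2) has one early discontinuation column, and Part 1 (Table 1-1) has a combined end-of-study and early discontinuation column. Neither has a visit, call or vital-status check after it. Section 8.3.1 says investigators need not actively look for adverse events once participation has ended. For subjects who cannot be reached, Section 7.3 adds: "Should the subject continue to be unreachable, he/she will be considered to have withdrawn from the study".

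On the analysis side, Table 9–2 defines the Part 2 full analysis set as everyone randomised: "Statistical analyses will be based on study treatment groups as per randomisation, irrespective of the study treatment actually received". Section 9.3 makes it the primary set for efficacy. Section 9.4.1 does not impute missing data unless otherwise stated. Table 3–2 sets time to sustained recovery, ventilation, ICU transfer and all-cause mortality over the 28-day follow-up.

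**The concern.** In a trial with repeated dosing, an investigator may have reason to stop treatment, and continued follow-up is then a separate decision. Here the dose is complete after Day 1. Tying exit from the study to exit from treatment leaves only one consequence: the clinical status score, oxygen and ventilation use, ICU transfer, survival and new adverse events are no longer recorded.

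An analysis of all randomised subjects needs those outcomes. Subjects withdrawn for safety may be less likely to recover than those who stay. If they are censored when they leave, the Kaplan-Meier estimate treats them as having the same future as subjects still under observation. The sustained-recovery definition adds a second route. Recovery must hold for 14 consecutive days, so a subject withdrawn within 14 days of first reaching level 3 cannot have it confirmed. A later analysis rule can choose how to treat the gap but cannot recover data that were never collected.

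**Working it through.** **1. Where the data stop.** Dosing ends on Day 1 (7.1). Investigator withdrawal ends participation (7.2). One visit is sought if possible (7.2), nothing is scheduled afterwards (Tables 1-1 and 1–2), and there is no duty to seek later events (8.3.1). Section 8.3 keeps the investigator responsible for following adverse events that led to discontinuation. Section 8.3.3 follows serious events and events of special interest to resolution. Neither collects the efficacy endpoints or new non-serious events.

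**2. The plan's own figures (Section 9.2, Table 9–1).** Hazard ratio per interval = ln(XVR011 ratio)/ln(placebo ratio):
- ln 0.50/ln 0.80 = 3.11
- ln(0.25/0.50)/ln(0.50/0.80) = 1.47
- ln(0.20/0.25)/ln(0.20/0.50) = 0.24

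All three match. Expected events: 408 × 0.85 × 0.80 = 277, against the stated 275. The event count therefore fits only if the 15% drop-outs (about 61 subjects: 41 XVR011, 20 placebo) contribute no events. With everyone followed, it would be 408 × 0.80 = 326. The protocol does not split the 15% by cause, so the share due to investigator withdrawal is unknown.

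**3. Cost per subject.** Each subject with unknown Day 29 vital status adds 1/272 = 0.37 points of uncertainty to XVR011 mortality, or 1/136 = 0.74 points to placebo mortality. The ceiling, with every planned drop-out unknown, is 15 points per arm. If one third were investigator withdrawals (assumed), it is 5 points.

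**4. Recovery estimate, if withdrawal is censored at the time (assumed).** Take withdrawal on Day 3, midway between Day 1 and Day 5.
- XVR011: S(3) = √0.50 = 0.707. Implied recovery by Day 7 = 1 − 0.25/0.707 = 0.646.
- Placebo: S(3) = √0.80 = 0.894. Implied recovery by Day 7 = 1 − 0.50/0.894 = 0.441.

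Suppose about 5% per arm (assumed: 14 of 272 and 7 of 136) are withdrawn and would not have recovered by Day 7. The overstatement is 14/272 × 0.646 = 3.3 points and 7/136 × 0.441 = 2.3 points. The net between-arm effect is about 1 point, against a planned Day 7 difference of 50% − 25% = 25 points.

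**5. Error rate under stress (simulation, 4,000 trials per case, unstratified log-rank).** Assumptions not taken from the documents: no treatment effect, both arms on the placebo curve, and a share of the eventual non-recoverers withdrawn in the first week and censored then.

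| Non-recoverers withdrawn, XVR011 / placebo | Subjects | One-sided error | Kaplan-Meier recovery, Day 29 (true 80%) |
|---|---|---|---|
| 50% / 50% | 41 | about 0.02 | 88% in both |
| 75% / 75% | 61 | 0.025 | 94% in both |
| 50% / 0% | 27 | 0.35 | differs by arm |
| 75% / 25% | 48 | 0.52 | differs by arm |
| 75% / 25%, followed to Day 29 | 48 | 0.024 | 80% in both |

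Balanced withdrawal distorts the recovery estimate but not the test. Marked imbalance damages the test, and continued follow-up removes the problem. The two high error rates shift with the assumed timing of withdrawal.

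**The case against.** **Size and safeguards.** The clause is permissive and such withdrawals may be few. Part 2 is double-blind, which makes strong imbalance between arms less likely. Earlier data are kept: after a withdrawal of consent for disclosure, "the Sponsor may retain and continue to use any data collected before such a withdrawal of consent". A subject withdrawn for an adverse event already counts in the any-event proportion. The censoring rule may be in the statistical analysis plan, so its absence from the protocol is no fault. All of this stands. It limits the size but does not restore uncollected outcomes.

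**Reasons for leaving the study.** Participation carries burdens beyond the infusion: blood samples, swabs, and medication restrictions to the end of study (Table 6–5). The investigator may have good grounds to end those. This also stands, so the point does not call for a ban on investigator withdrawal.

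**Stronger readings a reader might infer.**
- *That adverse events, protocol violations or pregnancy trigger withdrawal.* They appear only in a list introduced by "When a subject participation has been terminated prior to completing the study, the reason is recorded as follows". These are codes for an exit that has already happened, and the list also covers subjects who leave by choice.
- *That Section 7.2 contradicts the full analysis set.* That definition says who is analysed and in which arm, not how long they are followed. Withdrawn subjects stay in the denominator; some of their outcomes are unknown.
- *That it contradicts Section 10.5.4.* There, "The subject will be followed to determine the outcome of the pregnancy", generally no longer than 6 to 8 weeks beyond the estimated delivery date. That can run well past Day 90 and does not depend on the visit schedule, so both rules can be met.
- *That Section 7.3 merges loss to follow-up with withdrawn consent.* Section 7.2 codes them separately.

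**Conclusion.** The point holds as a data-collection gap. An investigator's withdrawal after the only dose ends outcome collection before Day 29, in a trial whose primary analysis takes in everyone randomised. The link to prognosis is plausible for safety withdrawals and weak for administrative ones. The intensive-care rule in Section 8.1.1 is a separate route out of the study and is not counted here.

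The protocol supports no single figure for the bias. It gives no withdrawal rate by cause, no balance between arms and no censoring rule for subjects withdrawn alive. Under the assumed 5% balanced withdrawal, the between-arm effect on Day 7 recovery is about 1 point, and equal withdrawal leaves the test close to its nominal level. Only strongly unequal, prognosis-linked withdrawal would undermine the test; those simulations are stress cases, not forecasts. This is a worthwhile, inexpensive improvement. It does not show that the planned analysis is invalid.

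**What to change.** Keep the investigator's discretion to withdraw a subject, and keep the list of recorded reasons. Amend Section 7.2 so that a subject withdrawn by the investigator who has not withdrawn consent is still followed for outcomes to Day 29: status on the 8-point scale, oxygen and ventilation use, ICU status, serious adverse events and vital status. Collection can be by visit, telephone or medical records, as consent permits. Show this in Tables 1-1 and 1–2 after the early discontinuation column.

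In Section 7.3, for subjects lost to follow-up, add an attempt to obtain Day 29 vital and hospital status from records where consent permits.

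The cost is a protocol amendment, a sentence in the consent form, and a small number of extra contacts or record checks. Dose, eligibility and clinical management are unchanged.

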### **7.3 Loss of Subjects to Follow-Up**

A subject will be considered lost to follow-up if he or she repeatedly fails to return for scheduled visits and is unable to be contacted by the study site.

The following actions must be taken if a subject fails to return to the clinic for a required study visit:

- The site must attempt to contact the subject and reschedule the missed visit as soon as possible (and within the visit window, where one is defined) and counsel the subject on the importance of maintaining the assigned visit schedule and ascertain whether or not the subject wishes to and/or should continue in the study.
- In cases in which the subject is deemed lost to follow-up, the Investigator or designee must make every effort to regain contact with the subject (where possible, 3 telephone calls and, if necessary, a certified letter to the subject's last known mailing address or local equivalent methods). These contact attempts should be documented in the subject's medical record.
- Should the subject continue to be unreachable, he/she will be considered to have withdrawn from the study.

Discontinuation of specific sites or of the study as a whole is handled as part of the appendix on Governance, Appendix 1, Section 10.1.9.

